## Non-inclusion criteria:

- 1. Other myasthenic syndromes, such as:
     - - Non-generalised myasthenias (ocular).
       - Lambert-Eaton syndrome.
       - Myasthenias associated with a malignant thymoma.
       - Hereditary myasthenic syndrome.
  2. Under 18 years old or over 70 years old
  3. Failure to sign the informed consent form
  4. Patient not affiliated with the social security regime
  5. History of severe allergic reaction or anaphylactic reaction to a murine monoclonal or humanised antibody, or known hypersensitivity to one of the components of rituximab.
  6. History of severe allergic reaction or anaphylactic reaction to methylprednisolone.
  7. Severe heart or pulmonary condition (in the opinion of the investigator: to be documented in the CRF).
  8. Presence of an uncontrolled concomitant disease, such as a condition affecting the central nervous system, kidneys, or liver, or an endocrine or gastro-intestinal condition, which in the investigator's opinion does not allow the patient to be included.
  9. Active infection of any kind. History of recurrent or chronic severe infection. History of deep infection related to fasciitis, abscess, osteomyelitis during the previous 52 weeks.
  10. Immunodeficiency syndrome, including seropositivity for HIV.
  11. Surgical operation scheduled in the year following possible inclusion.
  12. Any type of vaccination during the previous 28 days (it is advisable to seriously consider the indication of a vaccination (e.g. a flu vaccine for a patient suffering from a neuromuscular condition) prior to treatment with rituximab and to carefully assess the efficacy (which may be completely lost simply due to the action mechanism of rituximab). In other words, the need to vaccinate patients must be anticipated well in advance of 28 days prior to the rituximab injection. The use of a live attenuated vaccine is prohibited for the entire duration of the study (and for the 28 days prior to the study).
  13. Treatment with any experimental agent within 28 days of the infusion or at 5 half-lives of the drug in question (the longest of these two time frames is to be taken into account).
  14. Previous treatment (within one month of inclusion) with a cell depletion therapy, of any kind whatsoever, such as, for example, CAMPATH, anti CD4, anti CD5, anti CD3, anti CD19, anti CD11a, anti CD22, anti-Blys/BA.
  15. Positive serum beta hCG result at the screening or any other positive pregnancy test carried out before the first rituximab injection.
  16. Pregnancy or breast feeding or attempting to become pregnant during the study.

17.Positive **hepatitis B** test (positive Hbs antigen and/or positive PCR HBV).

However, patients presenting previous hepatitis that has been cured (AgHBS negative, Ac anti-Hbc +/-, Ac anti-Hbs+) can be included with specific monitoring for Ag  Hbs and PCR HBV every three months and 6 months after the end of the Study or **hepatitis C**.

18.Haemoglobin < 8.0 g/dL

19.Polynuclear neutrophil <1.5 X 10 ³/µL.

20.IgG and/or IgM levels < 5.0 and 0.40 mg /mL, respectively.

## 6 Treatment administered to study participants

## 6.1 Description of the treatments required to conduct the research

Rituximab chimeric monoclonal murine/human antibody obtained through genetic engineering. It is a glycosylated immunoglobulin combining the constant regions of a human IgG1as well as the heavy and light chain variable regions of murine origin.

A single-use bottle contains 500 mg/50 ml of rituximab.

Each ml of solution contains 10 mg of rituximab.

The prepared MabThera solution must be administered via intravenous infusion using a specific route. The diluted solution for IV infusion must not be injected rapidly or administered as a bolus.

## 6.2. Primary adverse reactions to rituximab (Mabthera®):

Intravenous administration of (Mabthera®), can cause a certain number of adverse reactions. One of the side effects, that occurs particularly during the first two hours following the first infusion, is characterised by fever, chills and tremors, sometimes combined with an outbreak of uticaria or even a drop in blood pressure and in the worst case difficulty breathing. Premedication (see below) intended to prevent these manifestations will be systematically administered when the medication is injected. Moreover, in order to minimise these reactions, the rituximab injection speeds will be gradually increased as it is administered (see Appendix 16.6, "Procedure for the intravenous administration of Mabthera").

Other possible adverse reactions are: pain (abdomen, chest, muscles, joints, injection sites), sensations of discomfort, changes in blood pressure.

Like immunosuppressants and corticosteroids, rituximab (Mabthera®) also presents a risk of infection, with a potentially addictive effect due to previous and concomitant exposure to immunomodulatory treatments. In particular, the risk of serious viral infections has been documented, whether primary infections or reactivations (e.g., EBV, VZV, etc.) or exacerbations (e.g., of the JC virus). Three cases of progressive multifocal leucoencephalopathy (PML) have been reported. This infection has been observed in lupus and vasculitis, where treatment also includes other immunosuppressants. To date, the causal relationship between rituximab (Mabthera®) and progressive multifocal leucoencephalopathy has not been established. However, the appearance of symptoms in the central nervous system must indicate a diagnosis of PML which must be substantiated by an MRI of the brain ± a lumbar puncture with screening for the JC virus by PCR.

## 6.3. Treatment regimen

### Rituximab dose:

The dose recommended by the Roche laboratory is the one used for treating rheumatoid arthritis (2): i.e., 2 injections of 1000 mg of Rituximab at an interval of 2 weeks.

A maintenance treatment in reorder to minimise the risk of a relapse (as for lymphoma (26)) will be carried out: one additional injection of 1000 mg of Rituximab in the 6th month after the previous injection (M6.5 (+/-8 days)).

### Premedication:

Corticosteroids: all patients will be given 100 mg of Methylprednisolone via slow IV, 30 minutes before the Rituximab injection in order to reduce the potential side effects.

Antipyretics: it is recommended that each patient receive premedication of 1 g (iv or by mouth) of Paracetamol, 30 to 60 minutes prior to the Rituximab infusion in order to reduce the potential side effects.

Antihistamines: it is recommended that each patient receive premedication with an H1 antihistamine (by mouth, e.g. Cetirizine, ZYRTEC: One 10 mg capsule), 30 to 60 minutes before the Rituximab infusion in order to reduce the potential side effects.

### Concomitant treatments: depending on the context:

1. plasma exchanges prior to the Rituximab injection may be authorised.
2. Concomitant corticosteroid treatment is authorised, up to one dose of 1 mg/kilo/day.
3. Bolus doses of Methylprednisolone are authorised.
4. Maintaining a treatment with immunosuppressants (methotrexate, cyclophosphamide, azathioprine, mycophenolate mofetil) or polyvalent immunoglobulins is recommended. However, we will try to limit combined treatments: corticosteroid treatment and one of the immunosuppressants listed above can be maintained (prescribed for longer than 6 months, if possible), to which rituximab will be added, but multiple combinations will be avoided.

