In patients who present an incomplete response or significant side effects from corticosteroids, the rule is to add immunosuppressive agents such as azathioprine, methotrexate, cyclophosphamide and/or cyclosporine A. The efficacy of these molecules has been shown in clinical trials with a limited number of patients, and with efficacy that is sometimes moderate (8, 10). Intravenous immunoglobulins or plasma exchanges can also offer a beneficial effect in these resistant forms of diseases, although their efficacy is short lived (11, 12).

Because some patients maintain resistance to all these treatments, and as some of them go on to develop side effects, new therapeutic approaches are necessary.

**Therefore, we are proposing an open, prospective, multi-centre, phase II pilot study to assess the efficacy of Rituximab for treating patients with inflammatory myopathy associated with specific antibodies or patients suffering from generalised myasthenia, and who are resistant to the conventional treatments.**

This first stage is necessary before a phase III trial, comparing corticosteroids to Rituximab in these indications.

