## 3.3. Benefits/Risks

The lives of the patients who must be included in the study are at risk due to 1) the severity of their diseases (myositis or myasthenia) which affect the oropharyngeal and respiratory muscles, and 2) resistance to the various immunomodulators tested. Rituximab - the efficacy of which will be tested here - is used as a salvage therapy. In our experience, the efficacy of rituximab is only evident after 8 to 16 weeks. Given these seriously ill patients and to cover rituximab's "silent" phase, it would not be ethical to stop any concomitant immunomodulatory treatment. This is why, at the investigator's discretion, associated immunomodulatory treatments are permitted and indeed recommended. Thus, maintaining corticosteroids in combination with methotrexate, cyclophosphamide, azathioprine, mycophenolate mofetil or polyvalent immunoglobulins is recommended. However, we will try to limit combined treatments: corticosteroid treatment and one of the immunosuppressants listed above can be maintained (prescribed for longer than 6 months, if possible), to which rituximab will be added, but multiple combinations will be avoided. The possibility of severe adverse reactions has been taken into consideration by the investigators, in particular after discussions with the Roche laboratory, which will provide the rituximab. The risk/benefit balance leans in favour of these combined treatments. Nonetheless, an **independent** **supervisory committee** (see § 8 regulatory aspects) tasked with monitoring all adverse reactions will meet after the inclusion of the first 4 patients. This committee will make the decision to proceed with the trial. One of the primary benefits expected if rituximab is effective, in addition to a clinical improvement for patients, will be to be able to gradually lighten the burden of combined treatments in patients who were initially at a therapeutic impasse.

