# 7 Statistics

## 7.1. Statistical analysis plan and justification for the number of patients to include:

**Myositides**

Twelve patients with inflammatory myopathy associated with anti-synthetases (JO-1, PL-7 or PL-12) and 12 patients with inflammatory myopathy associated with anti-SRP will be included in the study.

For each group of patients (anti-synthetase and anti-SRP), if efficacy is observed in at least 6 patients, it will be possible to conclude that the response rate is above 25% (limit lower than 90% of the confidence interval for an observed response rate of 50%).

For a given subject, efficacy is determined by an improvement in muscle strength, defined by at least a 2-point gain on the Kendall scale in at least 2 different muscle groups (i.e. a gain of at least 4 points) (18) (see Appendix 1), in the 12th month.

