**Myasthenias**

Twelve patients with generalised and refractory myasthenia with anti-RAch antibodies will be included in the study.

If success is observed in at least 6 patients, it will be possible to conclude that the response rate is above 25% (limit lower than 90% of the confidence interval for an observed response rate of 50%).

For a given subject, efficacy is determined by an improvement in muscle strength defined by at least a 20-point gain in the MMG score (47, 48) in the 12th month.

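### The primary response counts any M12 strength gain, even after a methylprednisolone bolus or a rise in immunomodulation, so in an uncontrolled trial such a patient counts as a rituximab success

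*Protocol*

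**What the plan says.** **Response.** Section 7.1 states for myositis: "For a given subject, efficacy is determined by an improvement in muscle strength", meaning a gain of at least 2 Kendall points in at least 2 muscle groups in the 12th month. For myasthenia, "efficacy is determined by an improvement in muscle strength defined by at least a 20-point gain in the MMG score", again in the 12th month. Section 3.2 repeats both definitions, and section 4.1 sets the comparison as M12 against D0. None of these places mentions treatment given in between.

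**Decision rule.** Each of the three groups has 12 patients. In section 7.1, "if efficacy is observed in at least 6 patients, it will be possible to conclude that the response rate is above 25" per cent. The justification given is the "limit lower than 90% of the confidence interval for an observed response rate of 50" per cent.

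**Permitted treatment.** Under concomitant treatments, section 6.3 states "Bolus doses of Methylprednisolone are authorised" and gives no number, dose or timing. It also allows daily corticosteroids up to 1 mg/kg. Section 3.3 says that, at the investigator's discretion, "associated immunomodulatory treatments are permitted and indeed recommended". Some limits are stated. Immunosuppressants or immunoglobulins are to be maintained, multiple combinations are to be avoided, and plasma exchange is named only before the injection.

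**Treatment changes as outcomes.** Sections 3.2 and 4.1 list immunomodulator doses, and for myasthenia the exacerbations needing hospitalisation or a steroid change, as secondary criteria only.

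**The concern.** The trial is open with a single treatment, and the count of responders is its only basis for an efficacy conclusion. If a patient deteriorates, receives a bolus or a higher steroid dose and reaches the strength threshold at M12, the definition records a success. The primary objective in section 3.2 then credits it to rituximab, and no comparison group shows how often this would happen without the drug.

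The protocol itself makes the scenario plausible. It expects exacerbations that need a steroid change. In section 2.1 it says that immunoglobulins or plasma exchange "can also offer a beneficial effect in these resistant forms of diseases, although their efficacy is short lived". A short-lived effect matters most when it falls close to the one visit that decides success.

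With 12 patients and a threshold of 6, the conclusion can turn on how one patient is classified.

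**Working it through.** **Inputs from the protocol.** n = 12 per group, success at 6 or more responders, reference rate 25%, 90% confidence interval (sections 3.2 and 7.1). I read the interval as two-sided, so the lower limit carries 5%.

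**Step 1. Reproduce the stated 25% limit for 6/12.**
- Exact (Clopper-Pearson), the 5% quantile of Beta(6, 7): 24.5%.
- Wald, 0.5 − 1.645 × √(0.5 × 0.5 / 12) = 0.5 − 0.237: 26.3%.
- Wilson: 28.6%.

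The protocol's 25% is reproduced to rounding, although the exact limit falls just below it.

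**Step 2. Operating characteristics of the rule.** With X binomial(12, p):
- P(X ≥ 6) at p = 0.25 is 5.4%, the false-success chance per group.
- P(X ≥ 6) at p = 0.50 is 61.3%, the power.

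**Step 3. Weight of one patient at the threshold.** If one of 6 responders owes the gain to escalation and is reclassified, the count is 5/12.
- Exact lower limit, the 5% quantile of Beta(5, 8): 18.1%.
- Wald, 0.4167 − 1.645 × √(0.4167 × 0.5833 / 12) = 0.4167 − 0.2341: 18.3%.
- Wilson: 22.0%.

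All three are below 25%, and 5 is below the required 6, so the conclusion is reversed. With two such patients the count is 4/12 and the exact limit is 12.3%. This step needs no assumed rate of escalation.

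**Step 4. Effect on false success, under an assumption.** Let the true rituximab response be 25%, and let a share r of true non-responders reach the strength threshold through added treatment. The protocol gives no value for r. The apparent rate is 0.25 + 0.75r, and the expected number of such patients per group is 12 × 0.75 × r = 9r.

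| r (assumed) | expected patients per group | apparent rate | P(X ≥ 6 of 12) |
| --- | --- | --- | --- |
| 0% | 0 | 25.0% | 5.4% |
| 5% | 0.45 | 28.75% | 9.9% |
| 10% | 0.9 | 32.5% | 16.1% |
| 15% | 1.35 | 36.25% | 24.1% |
| 20% | 1.8 | 40.0% | 33.5% |

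An average of about one such patient per group (r = 10%) roughly triples the false-success chance.

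**Step 5. Can existing data support a stricter definition?** Section 4.3 lists recording of related medications from D0 to D2 and at D7, D14, D21, M6.5, M12 and M18. It does not list this at D-1, so the reference level has to be the D0 record. No visit is scheduled between M6.5 and M12, so the dates of changes in that interval must be asked for explicitly.

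**The case against.** A reader might infer that rescue is unrestricted up to M12. The text does not support that. Section 6.3 caps daily steroids, speaks of maintaining rather than starting other agents, aims to avoid multiple combinations, and mentions plasma exchange only before the injection. Section 3.3 explains continued treatment as cover for the 8 to 16 weeks before rituximab acts, well short of M12. Background treatment that is merely continued is also present at D0, so a change score from D0 is exposed mainly to escalation. All of this stands. It narrows the gap to boluses, steroid increases under the cap and discretionary changes, but none of it alters how a patient who received these is counted.

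A reader might also infer that the bias always favours the drug. It need not. Steroid reduction is an intended benefit (sections 3.2 and 3.3), and tapering could lower strength in patients who respond. Section 2.1 also lists steroid-induced myopathy as a side effect.

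The size of r is open to challenge. Under section 5, patients must have had an inadequate response to, or not tolerated, corticosteroids and at least two other approaches, so rescue with the same agents may often fail to reach the threshold. This is fair: the values in step 4 are illustrative, whereas step 3 does not depend on them.

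Finally, response regardless of other treatment is a legitimate choice in a salvage pilot, escalation would be visible in the secondary criteria, and an analysis plan not at hand might add sensitivity analyses. But the protocol already fixes both the responder definition and the 6/12 rule, and the secondary summaries do not feed into that rule.

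**Conclusion.** The point holds in a limited form. The stated responder definition credits rituximab with M12 strength gains that may come from boluses or increased immunomodulation, and without a control arm nothing in the decision rule separates the two.

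The firm part of the size is the fragility at the threshold: one reclassified patient moves the exact lower limit from 24.5% to 18.1% and reverses the conclusion. The rise in false success from 5.4% to between 9.9% and 33.5% per group rests on two assumptions, a true response of 25% and a share of 5% to 20% of non-responders reaching the threshold through added treatment.

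The documents do not show that such escalation will be common or that the net bias must favour the drug. Nor is permitting background treatment the fault, since section 3.3 gives an ethical reason for it. The fault lies in the response definition. It should be corrected, because it governs the trial's only efficacy conclusion and the correction is cheap.

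**What to change.** Leave the permitted treatments unchanged and amend the analysis definition in sections 3.2, 4.1 and 7.1. Count a patient as a responder only if all of the following hold, protocol premedication aside:
- the strength criterion is met at M12;
- no immunomodulator has been started since D0 or is, at M12, above its level recorded at D0;
- no bolus, new immunoglobulin course or plasma exchange was given within a period before M12 whose length is fixed in advance.

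The second condition catches an earlier escalation that is still in place at M12, which a window between M6.5 and M12 would miss. Apply the 6/12 rule to this definition and report the strength-only rate beside it. Have the case report form capture the dates of such changes between M6.5 and M12.

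D21 strength should not serve as a check on non-rituximab effects, because it follows the methylprednisolone premedication at D0 and D14 and says nothing about late escalation.

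**Cost.** Some definition wording, a little programming and one added data item. The response rate may be somewhat lower, and some true responders who received a bolus would count as failures; the strength-only rate makes that visible.

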## Assessment of Rituximab's toxicity

In the randomised trial during rheumatoid arthritis, few serious side effects were observed (one case of high blood pressure, one case of pneumonia, one case of staphylococcus aureus septicaemia and one case of renal failure) (2).

The tolerance assessment will be carried out according to the usual clinical and biological monitoring criteria:

1. Clinical parameters: the clinical exam before and after the Rituximab injection will include blood pressure, respiratory rate, oxygen saturation (finger) and temperature, every 15 minutes for the first 2 hours then every 2 hours for the next 8 hours and finally 3 times a day for the 2 days following the first injection, and 8 hours for the 2nd injection. These parameters will also include a clinical exam once a day.
2. Biological parameters: the usual biological parameters (CBC, natremia, kalemia, chloremia, creatinemia CPK level, bilirubin, ALAT, ASAT, gamma GT, LDH, CRP) will be carried out before each Rituximab injection.
3. Immunological parameters: immuno-phenotyping including markers such as: CD19, CD20, CD4, CD25, CD45 RO, CD69, CTLA-4, CD40L, CD8 will be carried out at the same time.
4. Autoantibody titration will be carried out at the same time.

## Rules for stopping Rituximab (temporarily or permanently)

In the case of fever, chills, a drop in blood pressure or in saturation or breathing difficulties, the infusion will be stopped immediately and will not be resumed until medical approval has been given. The doctor shall determine the degree of severity.

In the case of a serious event (as defined below) which could be severe hypotension, severe dyspnoea with bronchospasm serious viral infection (primary infection, exacerbation (for example as EBV, VZV, etc.) or reactivation (PML for example), rituximab must be stopped permanently. The patient will remain in the study and will continue to be monitored as scheduled (see § 4.4 Rules for definitively or temporarily stopping the study).

In the case of mild to moderate reactions as listed below:

| **Flow rate** | **Fever** | **Chills** | **Congestion of the mucosa Oedema** | **Drop in systolic BP** |
| --- | --- | --- | --- | --- |
| **Reduce the flow rate by 50% if**  **one of these symptoms develops** | > 38.5°C | moderate | Moderate | > 30 mm Hg |

When the symptoms presented disappear, the infusion can resume but at a flow rate 50% lower than that which was in place before the symptoms appeared. **Monitoring after the incident must be carried out every 15 minutes for the first hour then every hour.**

# 7 Statistics

## 7.1. Statistical analysis plan and justification for the number of patients to include:

**Myositides**

Twelve patients with inflammatory myopathy associated with anti-synthetases (JO-1, PL-7 or PL-12) and 12 patients with inflammatory myopathy associated with anti-SRP will be included in the study.

For each group of patients (anti-synthetase and anti-SRP), if efficacy is observed in at least 6 patients, it will be possible to conclude that the response rate is above 25% (limit lower than 90% of the confidence interval for an observed response rate of 50%).

For a given subject, efficacy is determined by an improvement in muscle strength, defined by at least a 2-point gain on the Kendall scale in at least 2 different muscle groups (i.e. a gain of at least 4 points) (18) (see Appendix 1), in the 12th month.

